##### Autonomic and psychometric measurement

The mean change from baseline for autonomic and psychometric measurements will be assessed by heart rate variability (HRV) and perceived stress scale (PSS). HRV will be evaluated by the commercial device PowerLab Biomap ML132 (AD Instrument, Castle Hill, Australia) with a 400 Hz sampling rate. HRV measurements will be conducted according to the guidelines written by the task force of the European Society of Cardiology and the North American Society of Pacing and Electrophysiology [29]. The standard deviation (SD) of the NN interval, square root of the mean squared differences of successive NN intervals, Low frequency (LF), High frequency (HF), LF/HF ratio and Total Power will be evaluated. Developed in 1983 by Cohen [30], the PSS is a self-reported questionnaire that evaluates degree of the individual’s perceived stress with a 5 point-Likert scale consisting of 14 questions. The questionnaire was translated into Korean, and the reliability and validity of the Korean version of the PSS [31] was studied.

##### Quality of life

EQ-5D will be used to determine the quality of life of a patient with chronic neck pain. The mean change from the EQ-5D-5L baseline will be used for analysis. The EQ-5D is a standardized instrument to measure health outcomes that offers generic questions about quality of life as it relates to personal health status. We will use the Korean version of the EQ-5D [32].

##### Global assessment

The participants’ global assessment will be performed using the PGIC, a self-reported 7-point categorical scale used to evaluate the overall improvement after treatment [24]. Participants will be asked to evaluate themselves subjectively regarding the improvement of their symptoms at the 4th week compared to baseline by selecting one of the following seven options: 1) very much improved, 2) much improved, 3) minimally improved, 4) no change, 5) minimally worse, 6) much worse or 7) very much worse.

##### Semi-objective outcomes

Semi-objective outcomes, such as the PPT with a pressure algometer, consumption of rescue medicines and days of restricted activity, will be checked. PPTs will assess the bilateral levator scapulae, trapezius descendens and paravertebral of the 6th cervical spine [33] using a hand-held dial Pressure Algometer Device (Baseline Push Pull Force Gauge Model 12–0304 (Fabrication Enterprises Inc., New York, USA)). We will check three times at each point and use the mean value (kg/cm2). This device has good inter-tester reliability even when performed by inexperienced testers [34]. The rescue medication, a maximum 3 g of acetaminophen per day, will be allowed, and the dose between two groups will be assessed at 4 weeks. Days of restricted activity are known to be a semi-objective outcome that can evaluate subjective symptoms through digitization [35]. In this study we have modified the “restricted activity page” from “Current estimates from the National Health Interview Survey, United States, 1988” questionnaire to suit chronic neck pain patients. The participants will be asked to answer the following three questions: 1) “How many days during the last 2 weeks were you forced to spend more than a quarter of a day (approximately 2–3 h) lying down due to neck pain?” 2) “How many days during the last 2 weeks were you forced to miss work or school for more than a quarter of a day (approximately 2–3 h) due to neck pain?” 3) How many days during the last 2 weeks did you feel that daily activities were restricted for more than a quarter of a day (approximately 2–3 h) due to neck pain?” (exclude days answered in questions 1 & 2)

##### Biomarkers

Inflammatory/immunologic and stress biomarkers will be assessed at 1 and 4 weeks after randomization. Biomarkers of inflammation such as ESR and CRP; immunologic markers such as IL-1B, IL-6, TNF-α, IFN-γ; and stress markers such as serum cortisol were chosen according to previous research [36, 37]. Blood samples were collected from 10:00 to 11:30 am to minimalize the cortisol changes throughout the day.

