Many trials have been conducted to evaluate the effect of acupuncture on chronic neck pain. However, several limitations have hindered conclusions on the value of acupuncture for chronic neck pain. First, according to a recent systematic review, many acupuncture chronic neck pain studies report subjective outcomes related to pain and disability using tools such as the visual analogue scale (VAS) and the Neck Disability Index (NDI) [9]. However, the placebo treatment had higher clinical effects than no treatment when measured by a subjective continuous outcome variable [10]. Moreover, in pain treatment, subjective outcomes cannot avoid the risk of bias [11]. Second, while there are several reviews on the effectiveness of acupuncture in chronic neck pain, no accepted mechanism is known; though, the chronic neck pain might be related with immunologic or stress factors. A lack of biological plausibility is also one of the problems of acupuncture studies about pain [12]. Third, although a minimal clinical important difference (MCID) is important in interpreting the clinical relevance of trial results, almost no trial about acupuncture for chronic neck pain considered the MCID when designing and interpreting the clinical trials. Finally, in many acupuncture trials, the treatment protocol is different from daily medical practice. Therefore, the results do not correlate well with applied clinical practice.

In view of the limitations of previous studies, our study outlines several improvements. First, we adapted a Park sham device (PSD; Acuprime, Exeter, UK) that is a widely used, validated sham device in acupuncture research [13] to evaluate the efficacy of acupuncture treatment in chronic neck pain with semi-objective outcomes, such as the pressure pain threshold, consumption of rescue medication and days of restricted activity. Second, we will explore the mechanism of acupuncture treatment in chronic neck pain and if the efficacy is mediated by inflammation and stress reduction. Third, to evaluate the clinical relevance and statistical significance, the MCID will be used to design a research protocol and interpret the results of the trial. Finally, we will reflect clinical practice by applying the myofascial-meridian release acupuncture (MMRA) treatment protocol that is used at the Spine and Joint Clinical Center in Kyung Hee University Korean Medicine Hospital, which will increase the external validity.

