#### Study plan

After oral and written consent is obtained from each patient, subject information will be collected at the first visit. After a participant voluntarily consents to the study, they will be screened using inclusion/exclusion criteria at the first visit. If the participants take the pain medications, a ten-day wash-out period will be needed. At the end of the screening phase, if an eligible participant meets the study criteria with moderate (PI-NRS score range from 4 to 6) or severe (PI-NRS score range from 7 to 10) chronic neck pain, then the subject will be randomly allocated into 1 of 2 groups (the MMRA or sham acupuncture group) with a 1:1 allocation ratio. The MMRA group and sham acupuncture group will receive a total of 8 acupuncture treatment sessions during 4 weeks. MMRA acupuncture will be conducted at traditional acupuncture points, or ashi points, with deqi sensation. Sham acupuncture will be performed at non-acupuncture points without deqi sensation using a PSD. After a 4-week treatment, primary outcome measurements will be evaluated.

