### Randomization and Allocation Concealment

Random numbers will be generated by a computerized random number table generator through the stratified block randomization method of the SAS package (Version 9.4; SAS institute Inc., Cary, NC, USA) with a random block size. The random number table will be prepared by an independent, blinded statistician. Two block numbers will be randomly used to prevent allocation guessing by researchers. A stratified random number table will be generated according to the severity of chronic neck pain (PI-NRS score range from the 4 to 6 group vs the 7 to 10 group). The random number table file will be protected by a password, and the independent, blinded statistician, who is not involved in the recruitment, acupuncture treatment or assessment, will manage the table. A random allocation will be conducted at visit 1 to participants who provide informed consent. When a participant meets the inclusion criteria, the two types of treatment will be explained to him or her. Acupuncture will be explained as “classical acupuncture, typically used in Korean medicine clinics” and sham acupuncture as “non-classical acupuncture, rarely used in Korean medicine clinics” [14]. To ensure allocation concealment, the participants will be randomized according to the random number table by the independent researcher, and the allocated group information will be sent by an e-mail. The e-mail will be printed out and stored as a source document.

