### Intervention

The acupuncture treatment will be conducted by doctors of Korean medicine (DKMs) with more than 6 years of Korean medicine college education and at least 8 years of clinical experience.

To ensure the same conditions except for the needling components [15] between the groups, all the treatment procedures and regimens will be described in detail in pre-specified protocols and SOPs. A moderate interaction between the practitioners and participants is allowed: at each visit before the treatment, the practitioner will ask the participant about recent symptoms and improvements and record the answers in the patient chart; the practitioner will touch the subject’s neck to determine the pain sites according to meridian sinews; the participant will be allowed to inquire about the treatment without restriction, but the practitioner will not be allowed to give confident or positive encouragement in response to questions concerning a prognosis. This information will be given to the practitioners in workshops conducted before the study begins to ensure a standardization of the treatments. The MMRM and sham acupuncture groups will receive a total of 8 sessions (2 sessions per week) of acupuncture treatment for 4 weeks. Each acupuncture treatment will be performed after the acupuncture points are sterilized with a disposable 70 % isopropyl alcohol swab. During the treatment, the participant will lie in a prone position with a cushion under the chest to ensure a stable position.

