### Outcome measurement

The detailed outcome measurement time points are provided in Table 1.

**Table 1 Tab1:** Schedule for the treatment and outcome measurements

Visit	S	1	2	3	4	5	6	7	8
Week		1		2			3	4	
Informed consent	●								
Demographic characteristics	●								
Vital signs	●	●	●	●	●	●	●	●	●
Blood test	●								●
Medical history	●								
Inclusion/Exclusion criteria	●								
Conformity assessment	●								
Treatment expectancy questionnaire	●								
Random allocation		●							
Treatment		●	●	●	●	●	●	●	●
Prescription of rescue medicine		●							
PI-NRS		●	●	●	●	●	●	●	●
NDI		●							●
CROM		●							●
HRV		●							●
Perceived stress scale		●							●
EQ-5D		●							●
PGIC									●
Pressure pain threshold		●							●
Consumption of rescue medicine									●
Days of restricted activity		●							●
Blinding test		●							●
Safety assessment		●	●	●	●	●	●	●	●

Visit 1: within 4 weeks after screening, Visit 8: 4 weeks after Visit 1 (+6 days)

*CROM* Cervical Range of Motion, *NDI* Neck Disability Index; *PGIC* Patient Global Impression of Change, *PI-NRS* 11-point Pain Intensity Numerical Rating Scale, *S* screening visit

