#### Secondary endpoint

The secondary outcomes include a change from the baseline of clinical relevance for pain (ratio of change greater than 1.5 in PI-NRS and decrease greater than 30 % and 50 % on the PI-NRS), function (NDI and Cervical Range of Motion (CROM)), autonomic and psychometric measurements (Heart Rate Variability (HRV) and Perceived Stress Scale (PSS)), quality of life (EuroQol (EQ-5D)), global assessment (Patient Global Impression of Change (PGIC)), semi-objective outcomes (pressure pain threshold (PPT), consumption of rescue medicine, days of restricted activity), immunologic and stress markers and adverse events.

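### The text and Table 1 give different biomarker sampling times, and the text read literally leaves no pre-treatment sample

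*Protocol article*

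**What the plan says.** The Biomarkers section of the protocol article sets the sampling times for ESR, CRP, the cytokines and serum cortisol: "Inflammatory/immunologic and stress biomarkers will be assessed at 1 and 4 weeks after randomization". It also gives a morning window of 10:00 to 11:30 for the blood draw.

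Table 1, which the article presents as the detailed schedule of outcome time points, has one blood row. It is labelled only as a blood test and is marked at screening and Visit 8. There is no separate biomarker row. The footnote reads "Visit 1: within 4 weeks after screening, Visit 8: 4 weeks after Visit 1 (+6 days".

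The Randomization and Allocation Concealment section says "A random allocation will be conducted at visit 1 to participants who provide informed consent", and Table 1 marks the first treatment at the same visit. Under Intervention, both groups "will receive a total of 8 sessions (2 sessions per week) of acupuncture treatment for 4 weeks".

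The Secondary endpoint section opens with "The secondary outcomes include a change from the baseline of clinical relevance for pain" and continues the same list through to the immunologic and stress markers. The Background states the mechanism aim: "we will explore the mechanism of acupuncture treatment in chronic neck pain and if the efficacy is mediated by inflammation and stress reduction". The Discussion calls this analysis exploratory.

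The Study plan adds, for the screening phase: "If the participants take the pain medications, a ten-day wash-out period will be needed". The article does not say which blood sample is the biomarker baseline, or whether blood is drawn before or after any wash-out.

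**The concern.** The two places agree on the last sample and disagree on the first. The text names a sample after randomisation that the table does not contain. The table contains a screening sample that the text does not name. Staff cannot follow both.

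The first sample decides what the change score means. If it is drawn after treatment has started, any effect already present at that time is subtracted out. If it is drawn at screening, the biomarker change covers a different and longer period than the pain change it is meant to help explain. Table 1 first measures PI-NRS, NDI, CROM, HRV, PSS, EQ-5D, pressure pain threshold and restricted activity at Visit 1. Even within the stress domain, HRV and PSS would start at Visit 1 while cortisol would start at screening or a week into treatment.

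At stake are the between-arm comparison of biomarker change and, more so, the mediation question, which needs each participant's biomarker change and pain change to refer to the same period. A pre-treatment sample that was not taken cannot be recovered later.

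**Working it through.** The plan states no figure to reproduce on this point. The check sets the passages side by side and applies calendar arithmetic.

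**Inputs**
- Randomisation and first treatment: Visit 1, taken as day 0 (Randomization and Allocation Concealment; Table 1).
- Sessions: 8 in total, 2 per week (Intervention).
- Screening: up to 4 weeks = 28 days before Visit 1 (Table 1 footnote).
- Visit 8: 4 weeks after Visit 1, plus up to 6 days, so day 28 to day 28 + 6 = 34 (Table 1 footnote).
- Blood row: screening and Visit 8 only (Table 1).

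**Reading 1: the text, literally.** The first sample is at about day 7. At 2 sessions per week, about 2 sessions have been given, and 2 / 8 = 25% of the course. Write D1 and D4 for the between-arm differences in a marker at week 1 and week 4. The comparison of change scores then estimates D4 − D1, not D4. The two agree only if D1 = 0, that is, if the first sessions have no effect on the marker. Table 1 has no blood mark at any visit about one week after Visit 1.

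**Reading 2: the text, loosely.** Table 1's week row labels Visit 1 as week 1, so the text may mean Visit 1 and the final visit. If blood is then drawn before treatment, no sessions precede the first sample and the 25% falls away. Table 1 still has no blood mark at Visit 1, so the conflict remains.

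**Reading 3: Table 1 governs and its blood row is the biomarker draw.**
- Biomarker interval, longest: 28 + 28 + 6 = 62 days.
- Interval for pain, HRV and PSS: 28 to 34 days.
- Excess of the biomarker interval: at most 62 − 34 = 28 days.

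The sample precedes randomisation. A shift between screening and Visit 1 that is common to both arms, c, enters both mean changes and cancels: (change in MMRA + c) − (change in sham + c) = difference in changes. Variation of that shift between participants does not cancel. It adds noise and weakens the within-person link between biomarker change and pain change.

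**Reading 4: Table 1's blood row is a screening and safety panel.** The 62-day figure then does not apply. The biomarkers are instead absent from the schedule of outcome measurements.

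Under each of the four readings, the text and the table fail to match.

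**The case against.** A reader might infer that neither version offers a usable baseline. The documents do not support that for Table 1. A screening sample comes before randomisation and before any needle, and it is comparable between arms in expectation. Its weaknesses are the gap of up to 28 days and its undefined relation to the wash-out.

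A reader might also infer that stopping analgesics contaminates the biomarker change. The article does not order the blood draw relative to the wash-out, and it speaks of pain medication without naming anti-inflammatory drugs. One exclusion criterion bars participants medicated for neck pain within the last 2 weeks. How many participants could be affected is therefore unknown, and a withdrawal shift would on average be similar in both arms.

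The 25% and the 62 days are alternatives that rest on different readings; they are not two faults of one plan. The 62 days should be set against 28 to 34 days for pain, since the same Visit 8 window applies to both.

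The link to change from baseline can also be questioned. The Biomarkers section says only that the markers will be assessed, and the secondary outcome list also contains items with no baseline value, such as the global impression of change and adverse events. That is fair, but change from baseline remains the natural reading of the list, and two samples per participant suggest that a change is intended.

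Finally, the mechanism work is labelled exploratory, and the primary endpoint does not depend on blood. This limits the severity. It does not remove the mismatch, for which no reconciling reading was found.

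**Conclusion.** The point stands as an internal inconsistency of moderate severity. Taken at its word, the text gives a first sample after about 2 of 8 sessions and no pre-treatment value. This figure assumes the literal reading and the stated two sessions per week. Under Table 1 there is a valid pre-treatment sample, but the biomarker interval may reach 62 days against 28 to 34 days for pain, HRV and PSS. That figure assumes that the blood row is the biomarker draw and that the full screening window is used.

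The consequence under Table 1 is mainly noise and misalignment with the pain change, not bias between the arms. The effect is confined to the biomarker outcomes and the exploratory mediation question. The primary PI-NRS analysis and the sample size are untouched.

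**What to change.** State one schedule in both the Biomarkers section and Table 1.
- Give the biomarkers their own row in Table 1.
- Name the baseline sample and draw it before the first treatment, preferably at Visit 1 so that it matches the other change outcomes. Take the second sample at Visit 8. Keep both within the existing 10:00 to 11:30 window.
- State how the baseline draw relates in time to any wash-out.
- If the screening blood test is a safety panel, label it so.

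The article expects recruitment to begin in November 2015, was published in February 2016 and describes blood collection in the past tense, so participants may already be enrolled. In that case, state which samples were actually taken and when, and use only pre-treatment samples as baseline. If the draw is moved during the trial, report the two baseline definitions separately so that they are not mixed unmarked.

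The cost is a correction of text and table with notification of the IRB, and at most one sample moved to another visit. The sample size and the primary analysis do not change.

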#### Safety and adverse events outcomes

All unexpected and unintended responses that are not necessarily related to the acupuncture treatment will be recorded at every visit on an adverse event report form by the practitioners and the participant. Adverse events known to be related to acupuncture treatments include pain, bruising, bleeding, dizziness, anxiety and infection [38]. A causal relationship between the acupuncture treatment and adverse events will be evaluated using a 6-grade scale (1 = definitely related, 2 = probably related, 3 = possibly related, 4 = probably not related, 5 = definitely not related and 6 = unknown), and the seriousness of the adverse events will be scored using a 4-point scale (1 = mild, 2 = moderate, 3 = severe and 4 = extremely severe).

#### Blinding assessment

The allocation guessing about real and sham acupuncture treatments will be assessed after the first treatment and at the end of the treatment. The participants will select questionnaires on their feelings about the acupuncture treatments using the following three questions: “classical acupuncture typically used in Korean medicine clinics”, “non-classical acupuncture, rarely used in Korean medicine clinics” or “don’t know”. The Credibility rating for both treatments will be evaluated using a credibility test with a 7-point Likert scale developed by Vincent et al. after their first treatment and at the end of the treatment [39]. The participants will rate the scores (0 = very low confidence and 6 = very high confidence) for the following four questions, “How confident do you feel that this treatment can alleviate your chronic neck pain?”; “How confident would you be in recommending this treatment to a friend who suffered from a similar complaint?”; “How logical does this treatment seem to you?”; “In your opinion how successful may this treatment be in alleviating other complaints?”

### Sample size calculation

The primary outcome of our study is overall neck pain, which is measured by the PI-NRS change from baseline to 4 weeks. In chronic neck pain, the minimum clinically important difference (MCID) is a 1.5 unit change in the PI-NRS score [25]. According to a previous study [40], we assumed that the SD of PI-NRS change from baseline to 4 weeks will be 1.88 in the treatment group and 2.21 in the control group, each with a population correlation between the baseline and follow-up scores that was estimated as 0.5. In a superiority test, we assumed that the PI-NRS difference between the two groups will be 1.5, which is identical to the MCID. With a 5 % of significance level (α = 0.05, 2-sided) and 80 % power (1-ß = 0.8), the sample size was calculated as 31 participants in each group using G*Power 3.13 software (Franz Faul, Universität Kiel, Germany). Considering a 15 % drop-out rate, a total of 74 participants is needed.

